## Methods and analysis

### Study design

This study is a cluster-randomised trial to determine the impact of two interventions on parasite carriage, gametocyte carriage and infectiousness to mosquitoes. A total of 180 compounds (consisting of three to six enrolled participants) will be randomised to one of three study arms (60 compounds per arm): arm 1 - current standard of care with passively monitored malaria infections; arm 2 - standard of care plus enhanced CCM; or arm 3 - standard of care and enhanced CCM, plus monthly screening and treatment (MSAT), as detailed in box 1.

Box 1Study armsArm 1 (control): Standard of careStandard of care with passively monitored malaria incidence at local health facilities. Health facilities will be equipped with research staff and adequate supplies to ensure malaria diagnosis and treatment with the first-line antimalarial artemether-lumefantrine (AL) according to national guidelines.Seasonal malaria chemoprevention (SMC) in children <5 years of age implemented by the National Malaria Control Programme (monthly treatment with sulfadoxine-pyrimethamine + amodiaquine from July to October).Arm 2 (intervention): community case management (CCM)Standard of care (as in arm 1).SMC (as in arm 1).Enhanced CCM for malaria involving weekly active screening for fever using a research-grade thermometer by a trained health worker. A measured temperature ≥37.5°C or reported fever in the last 24 hours will prompt screening with a conventional rapid diagnostic test (RDT). RDT-positive individuals will be treated with AL according to national guidelines.Arm 3 (intervention): CCM + monthly screening and treatment (MSAT)Standard of care (as in arms 1 and 2).SMC (as in arms 1 and 2).Enhanced CCM (as in arm 2).MSAT regardless of symptoms with a conventional RDT. Screening will be performed by research staff with 25–35 days between screening rounds; RDT-positive individuals will be treated with AL according to national guidelines.

The study will take place over approximately 18 months covering two high-transmission seasons and the low-transmission season (dry season) in between. Throughout the study, entomological monitoring will take place to evaluate the local mosquito population and potential exposure to infected mosquitoes.

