### Procedures

#### Study visits

At the start and end of each season, a cross-sectional survey will be performed concurrently in all enrolled compounds (online supplementary figure S1). These surveys will also include adults that are present in enrolled compounds but not participating in the interventions; additional informed consent will be obtained for this. In these surveys all individuals will have their axillary temperature measured and a finger prick blood sample taken for molecular assessment of gametocyte and parasite carriage (as detailed in table 1). In case of measured fever, the same finger prick blood sample will be used for malaria diagnosis by conventional RDT (first response malaria RDT, specific for *P. falciparum* and/or *P. vivax, P. ovalae* and *P. malariae*) and treatment will be offered as per national guidelines. Routine surveys will be conducted throughout the wet and dry seasons to assess parasite carriage, gametocyte carriage and infectivity to mosquitoes. These surveys will be performed on a subset of compounds each week on a rolling basis, so that each compound will be visited every 10 weeks. Finger prick blood samples will be taken and processed as detailed in table 1; one whole blood aliquot will be processed immediately for molecular detection of *P. falciparum* parasitaemia by quantitative PCR (qPCR) targeting varATS.^23^ qPCR-positive individuals (ie, those with parasites, not necessarily gametocytes) will be invited to donate blood for mosquito-feeding assays. The maximum number of feeding assays per day will be dependent on logistical feasibility. Asymptomatic infections that are detected by PCR will not be treated if unaccompanied by malaria symptoms, in line with national treatment guidelines. Routine surveys will continue throughout the dry season to allow a detailed assessment of the number of newly acquired infections when minimal exposure to infected mosquito bites is assumed.

10.1136/bmjopen-2019-030598.supp1Supplementary data

**Table 1 T1:** Sampling schedule; the table indicates the samples collected at each participant survey/visit

Sample type/procedure	Cross-sectional survey	Routine survey	Passive case detection	CCM	MSAT	DMFA
Axillary temperature and clinical assessment	X	X	X	X	X	
Dried blood spot (DBS)	X	X	X	X*	X	
Whole blood in RNA protect	X	X	X	X*	X	X
Whole blood for DNA	X	X	X	X*	X	X
Rapid diagnostic test (RDT)	X*		X	X*	X	
Highly sensitive RDT (HS-RDT)						X
Plasma						X
Blood smear			X†	X†	X†	X

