*Sampling only takes place if the subject has fever or history of fever in the last 24 hours.

†Sampling only takes place if the subject has a history of antimalaria treatment in the previous 3 weeks for microscopic confirmation of malarial infection.

CCM, enhanced community case management; DMFA, direct membrane feeding assay; MSAT, monthly screening and treatment.

In all three arms, clinical malaria episodes will be passively monitored at the local health facilities. Participants will be identified using study identity cards; for suspected malaria cases, temperature and clinical history will be recorded. Finger prick blood samples will be taken as detailed in table 1. Malaria diagnosis will be performed by RDT and infected subjects will be treated with artemether-lumefantrine (AL). For infections detected by community health workers during enhanced CCM (arms 2 and 3) or MSAT (arm 3) visits, the same procedure is used and samples are collected as detailed in table 1. For RDT or microscopy-positive infections detected at local health facilities or during the CCM or MSAT visits, when logistically feasible, the individuals will be invited to donate a blood sample for mosquito-feeding assays prior to treatment. For all mosquito-feeding assays blood samples will be collected and transported in a portable incubator or thermos flask to the insectary for direct membrane feeding assays (DMFAs).

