Box 3Objectives and end pointsPrimary objective/end pointParasite prevalence and density between arms by molecular detection at the end of the study cross-sectional survey (time frame: month 18 (end of second transmission season; January–February 2020)).Secondary objectives/end pointsParasite prevalence and density by molecular detection at the end of year 1 cross-sectional survey (time frame: month 6 (end of first transmission season; January–February 2019)).Parasite prevalence and density by molecular detection at the end of the dry season cross-sectional survey (time frame: month 12 (prior to second transmission season; June 2019)).Gametocyte prevalence and/or density by molecular methods at the end of study cross-sectional survey (time frame: month 18 (end of second transmission season; January–February 2020)).Gametocyte prevalence and/or density by molecular methods at the end of year 1 cross-sectional survey (time frame: month 6 (end of first transmission season; January–February 2019)).Gametocyte prevalence and/or density by molecular methods at the end of the dry season cross-sectional survey (time frame: month 12 (prior to second transmission season; June 2019)).Gametocyte prevalence and/or density by molecular methods among *Plasmodium falciparum* infections during all visits in the study (time frame: throughout study, an average of 18 months).The number of incident infections/clinical incidence detected during community case management involving active weekly fever screening, monthly screening and treatment, and passive case detection (time frame: throughout study, an average of 18 months).Infectivity to mosquitoes of *P. falciparum* infections (time frame: throughout study, an average of 18 months).Exploratory objectives/end points:The detectability of infections by highly sensitive rapid diagnostic tests (time frame: throughout study, an average of 18 months).The relationship between the proportion of infected mosquitoes and gametocyte density (time frame: throughout study, an average of 18 months).The impact of infection characteristics on the transmissibility of infections to mosquitoes (time frame: throughout study, an average of 18 months).The impact of human host characteristics on the transmissibility of infections to mosquitoes (time frame: throughout study, an average of 18 months).Association between total parasite density and gametocyte density (time frame: throughout study, an average of 18 months).Malaria transmission potential based on measured gametocyte densities and the association between gametocyte density and mosquito infection rates (time frame: throughout study, an average of 18 months).Number of acquired clones based on genotyping (time frame: throughout study, an average of 18 months).The duration of infections in the dry season (time frame: months 6–12, between end of season survey January/February 2019 and end of dry season survey June 2019).To quantify mosquito exposure in relation to incident infections and transmission opportunities (time frame: throughout study, an average of 18 months).

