
### Data analysis

For primary and secondary end points, parasite and gametocyte prevalences will be compared between arms using multivariate mixed-effects logistic regression models; parasite and gametocyte density will be assessed using multivariate mixed-effects linear regression models on log-transformed values. The number of incident infections will be assessed by Poisson regression and compared between arms. The proportion of infectious participants and proportion of infected mosquitoes will be assessed by logistic regression models. Analyses will take account of correlation of outcomes at the compound level and the matched randomisation scheme. There may be issues with convergence in mixed-effects models given the small number of subjects per compound. In this case, analysis based on compound level summaries will be performed. For exploratory end points, detected infections will be analysed in relation to the time and duration of infection, parasite and gametocyte prevalence and density, symptoms, complexity of infection, host characteristics, mosquito exposure and infectiousness to mosquitoes. Parasite density will be related to detectability by HS-RDTs. The association between gametocyte density and mosquito infection prevalence and intensity will be determined using an established Bayesian hierarchical model that incorporates the density of male gametocytes and gametocyte sex ratio.^40^ In exploratory end points, model fitting will be performed for different strata of infection characteristics (eg, complexity of infection, concurrent asexual parasite density and season) and host characteristics (eg, antigametocyte immune responses, age). Mosquito exposure by indoor and outdoor trapping methods will be associated with the likelihoods of incident infections and opportunities to transmit infections using comprehensive malaria transmission models.^41^

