### Sample size calculations and predicted impact of interventions

The hypothesis of the current study is that the parasite prevalence is considerably reduced in arms 2 and 3 compared with the standard of care. Assuming a conservative parasite prevalence of 40% in the control arm, the current sample size should be sufficient to detect a twofold reduction in parasite prevalence with >99% power. This sample size will also allow us to detect the anticipated difference in the proportion of infections that are gametocyte-positive at the moment of detection (secondary objectives 3–5). We assume that ≥80% of all infections detected in cross-sectional surveys (ie, chronic asymptomatic infections) concurrently carry gametocytes.^14^ We expect that infections that are detected by CCM or MSAT visits in arms 2 and 3 are of shorter duration and have lower gametocyte prevalence and density.^15^ If we assume ≤50% gametocyte prevalence among these CCM/MSAT-detected infections, monitoring 100 survey-detected and 100 CCM/MSAT-detected infections will result in 99% power to detect this difference (the calculations assumed a coefficient of variation of 0.5 and a significance level of 0.05).

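### Gametocyte carriage among infections from all visits is compared between arms that find infections by different routes; infectivity has the same problem if it is compared by arm

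*Protocol article*

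**What the plan says.** All places are in the protocol article.

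- **Aim (Study design):** the trial is "to determine the impact of two interventions on parasite carriage, gametocyte carriage and infectiousness to mosquitoes".
- **End points (Objectives/end points, Box 3):** the sixth secondary end point is gametocyte prevalence and/or density among P. falciparum "infections during all visits in the study". The eighth is infectivity of P. falciparum infections to mosquitoes over the whole study. Neither is limited to one type of visit.
- **Analysis (Data analysis):** for primary and secondary end points, "parasite and gametocyte prevalences will be compared between arms using multivariate mixed-effects logistic regression models". On infectivity: "The proportion of infectious participants and proportion of infected mosquitoes will be assessed by logistic regression models". Analyses are to allow for compound and for the matched randomisation. Detection route is not mentioned.
- **Route common to all arms (Study visits):** at routine surveys, "qPCR-positive individuals (ie, those with parasites, not necessarily gametocytes) will be invited to donate blood for mosquito-feeding assays". The surveys roll over subsets of compounds, "so that each compound will be visited every 10 weeks". Clinics also detect infections passively in all arms.
- **Routes that depend on arm (Box 1; Study visits):** weekly CCM exists only in arms 2 and 3, and MSAT only in arm 3. Feeding assays follow from these too: "For RDT or microscopy-positive infections detected at local health facilities or during the CCM or MSAT visits, when logistically feasible", the person is invited to give blood before treatment.
- **Expected difference by route (Sample size calculations and predicted impact of interventions):** at least 80% gametocyte carriage in infections found at cross-sectional surveys. For the others: "If we assume ≤50% gametocyte prevalence among these CCM/MSAT-detected infections", 100 infections of each kind give 99% power.

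**The concern.** Taken together, the definition and the analysis sentence place arm 1 infections, found at surveys and clinics, against arm 3 infections, found at surveys, clinics, weekly fever visits and monthly screening. The plan expects infections found by the last two routes to be younger and to carry fewer gametocytes when found. Arm 3 could therefore show lower carriage per infection even if the intervention changed carriage in no infection of any given type. The result would be read as an effect on transmissibility, which the article presents as the study's novel contribution.

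A second difficulty applies to both end points: their denominator is infected people, and the interventions are meant to change who is infected. The groups compared are selected after randomisation, and a participant who is uninfected because of the intervention does not count in its favour.

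**Working it through.** **1. Reproduce the plan's figure.** Inputs from the sample size section: 80% v 50%, 100 infections per group, alpha 0.05 (two-sided assumed). The mean proportion is 0.65.

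z = [0.30 − 1.96 × √(2 × 0.65 × 0.35 / 100)] / √[(0.80 × 0.20 + 0.50 × 0.50) / 100] = (0.300 − 0.132) / 0.0640 = 2.62, so power is 0.996.

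The stated 99% reproduces for independent infections. The contrast it powers is between detection routes, not randomised arms. The section ties it to secondary objectives 3–5. In Box 3 order those are the cross-sectional gametocyte end points, which contain no CCM/MSAT-detected infections; the all-visits end point is the sixth.

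**2. Arm difference from mix alone.** Suppose carriage within each route is the same in every arm: 80% if survey-detected, 50% if detected early. Let e be the share of an arm's infections detected early. Then

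pooled carriage = 0.80 × (1 − e) + 0.50 × e = 0.80 − 0.30 × e,

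and arm 1 minus arm 3 = 0.30 × (e₃ − e₁). Because the plan's figures are at least 80% and at most 50%, 30 points is the smallest route gap it allows for.

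**3. Arm 1 with no early-detected infections (e₁ = 0, carriage 80%).** The documents give no shares, so a range is shown. The last two columns give the chance of a significant arm difference from mix alone, for independent infections, two-sided 0.05, and assumed numbers per arm.

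| CCM/MSAT share in arm 3 | Arm 3 carriage | Odds ratio v arm 1 | 100 per arm | 200 per arm |
|---|---|---|---|---|
| 10% | 77.0% | 0.84 | 7% | 11% |
| 25% | 72.5% | 0.66 | 24% | 42% |
| 50% | 65.0% | 0.46 | 66% | 92% |
| 75% | 57.5% | 0.34 | 94% | >99% |

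**4. Arm 1 with clinic-detected infections.** Assume that 20% of arm 1's infections come from clinics and that these carry 50%. Arm 1 becomes 0.80 − 0.30 × 0.20 = 74%.

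- If 50% of arm 3's infections are CCM/MSAT-detected and the rest survey-detected, arm 3 is 65%. The gap is 0.30 × (0.50 − 0.20) = 9 points, odds ratio (0.65/0.35) / (0.74/0.26) = 0.65.
- If clinics also supply 20% of the remaining half in arm 3, then e₃ = 0.50 + 0.10 = 0.60 and arm 3 is 62%. The gap is 12 points, odds ratio 0.57, with a 44% chance of significance at 100 per arm and 73% at 200.

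**5. Sampling intensity.** Over 18 months (78 weeks) a compound enrolled from the start has about 78/10 ≈ 8 routine surveys. Arm 3 adds about 18 MSAT rounds and arms 2 and 3 about 78 weekly fever checks. This does not give the shares, but it makes a negligible CCM/MSAT share in arm 3 hard to assume.

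**6. Common-trigger comparison.** With survey-detected infections only, or within each route, the same inputs give 80% v 80%, odds ratio 1.00.

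**The case against.** - **The infectivity sentence states no arm comparison.** That is correct. It says only that the proportions are assessed, whereas the gametocyte sentence compares arms explicitly. For infectivity, the comparison is inferred from the aim and from the allowance for matched randomisation. That part of the point is conditional.
- **The authors know that routes differ.** They power a contrast between routes, and the full protocol or SAP could adjust for route, since the models are described as multivariate without listed covariates. Missing covariates would be no finding. But the sixth secondary end point as published pools all visits, and the analysis sentence compares it between arms, so a later plan would have to narrow that definition.
- **A reader might infer that the plan nowhere credits people being uninfected.** The documents do not support this. Three secondary gametocyte end points use cross-sectional surveys of all participants, at the same times and with the same test in every arm; uninfected people can count there as non-carriers. Transmission potential is also listed as exploratory.
- **A reader might take 15 points as the bias, or carry 80% v 50% over to infectivity.** Neither is supported. The 15 points need an assumed 50% share and no clinic-detected infections in arm 1, although clinics detect in all arms. The 80% and 50% are gametocyte prevalences; no infectivity rate by route is given. RDT-positive infections may be denser than those found only by qPCR, so even the direction is open.
- **Early detection is the intended mechanism.** This is partly right. But carriage when an infection is found is not carriage across an arm's infections. If early treatment prevents chronic carriage, surveys on a common schedule will show it.

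**Conclusion.** The point holds for the all-visits gametocyte end point: followed literally, the plan compares arms on infections collected by arm-specific routes that it expects to differ in carriage. It holds conditionally for infectivity, if arms are compared as the aim implies. Both end points also condition on infection after randomisation.

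For gametocyte prevalence the size is 30 points times the between-arm difference in early-detected share. At an assumed 50% CCM/MSAT share in arm 3, this is 15 points with no clinic-detected infections in arm 1. It is 9 points if 20% of arm 1's infections are clinic-detected with 50% carriage and arm 3's remaining infections are survey-detected. The route figures are the plan's; the shares and the clinic carriage are assumptions. For infectivity neither size nor direction can be derived.

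The primary end point and the three cross-sectional gametocyte end points are not affected. As only secondary end points are involved, this should be fixed but does not threaten the main result.

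**What to change.** - **Gametocyte carriage:** make between-arm comparisons only at the cross-sectional and routine surveys.
- **Infectivity:** make between-arm comparisons only from routine-survey feeding assays, which have the same schedule and qPCR trigger in all arms. The article describes no feeding assays arising from the cross-sectional surveys.
- **Denominator:** use all surveyed participants and count qPCR-negatives as non-infectious. Weight fed positives up to represent qPCR-positives not fed because of capacity. Such weighting is one reasonable choice; it assumes that those fed resemble those not fed at the same time, and it should be stated in advance.
- **Clinic-, CCM- and MSAT-detected infections:** report these by detection route, as description. The comparison of survey-detected with CCM/MSAT-detected infections can stay, labelled as a comparison of routes and tied to the correct secondary end point.

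The cost is a change of wording; no new data are needed. Fewer feeds enter the between-arm comparison, so its precision falls. The other feeds remain available for the exploratory models.

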### Sample size calculations and predicted impact of interventions

The hypothesis of the current study is that the parasite prevalence is considerably reduced in arms 2 and 3 compared with the standard of care. Assuming a conservative parasite prevalence of 40% in the control arm, the current sample size should be sufficient to detect a twofold reduction in parasite prevalence with >99% power. This sample size will also allow us to detect the anticipated difference in the proportion of infections that are gametocyte-positive at the moment of detection (secondary objectives 3–5). We assume that ≥80% of all infections detected in cross-sectional surveys (ie, chronic asymptomatic infections) concurrently carry gametocytes.^14^ We expect that infections that are detected by CCM or MSAT visits in arms 2 and 3 are of shorter duration and have lower gametocyte prevalence and density.^15^ If we assume ≤50% gametocyte prevalence among these CCM/MSAT-detected infections, monitoring 100 survey-detected and 100 CCM/MSAT-detected infections will result in 99% power to detect this difference (the calculations assumed a coefficient of variation of 0.5 and a significance level of 0.05).

Simulations predict that enhanced CCM will reduce asexual parasite carriage in arm 2 by 70%, 60% and 30% in children under 5 years, 5–15 years and adults >15 years, respectively. The addition of MSAT in arm 3 is predicted to have minimal impact in all age groups (figure 5). Simulations were carried out in Epidemiological MODeling software (EMOD) V.2.15^42 43^ an agent-based model of malaria transmission using within-host infection, immunity and infectivity dynamics^41 44^ calibrated to field data.^45^ The study site census was gridded into 1 km grid cells with a total human population of 7800 individuals and birth and death rates of 39 per 1000 per year, resulting in 17% of the population being under 5, and 25% between 5 years and 15 years. Within a grid cell, the biting rate is surface area dependent but otherwise homogeneous. Humans moved between grid cells at a rate of one trip per person per year, and each trip lasted on average 2 days. Vectors did not move between grid cells. Malaria dynamics are simulated in a highly seasonal setting with an annual entomological inoculation rate (EIR) of 150 in the presence of insecticide treated bed nets (ITNs). Seasonality was based on entomology data collected in 2011. The vector population was modelled as *Anopheles gambiae* mosquitoes with 65% anthropophily and 90% indoor feeding. All grid cells had the same seasonality and transmission intensity. For the simulations, the number of individuals per arm was ~165 during phase I until January 2019 when numbers increased by ~200 individuals per arm for phase II. Means of 500 stochastic realisations are shown. Simulated interventions are as follows:

